### Concurrent medical care

Participation in the study does not interfere with receipt of prescribed medications, medical devices or surgical procedures at any time point during the study. Diagnostic tests such as duplex ultrasound of the upper arm vasculature pertaining to an AV access will be part of standard care. Any adjuvant procedures required for the vascular access will be conducted as deemed necessary by the treating team. Findings from diagnostic tests (e.g., CT venogram, MR venogram) and procedural imaging (e.g., fistulogram) are logged in centralized REDCap study database.

## Statistical methods

### Sample size calculation and power considerations for primary outcome

The sample size estimate is based on the primary hypothesis that, by the end of the study, the patients in the AVG group will have more CVC-free days than patients in AVF group. Based on our pilot study [19, 20, 30], the average rate for CVC-free days was 15/100 patient-days among study patients who underwent AVF placement; similar or higher rate of CVC-free days was reported in other studies [31–33]. For this study, sample size calculations are based on two-sided tests with 5% type 1 error rate and a conservative estimate of 25% drop-out rate. Assuming a Poisson distribution and an average follow-up of two years, we will have > 90% power to detect a minimum of 5% points increase in CVC-free days in the graft group with 131 patients per group. We also considered situations where overdispersion is present for CVC-free days. With a total sample of 262 and 15/100 patient-days in the fistula group, we will have 80% power to detect an effect size of 25% for a 5% inflation of variance. The power will be greater if the rate of CVC-free days is 20/100 patient-days or higher in the fistula group.

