Until recently, the consensus guidelines on vascular access strongly preferred AVFs over AVGs, as in some populations AVFs have a longer secondary patency for dialysis and require less frequent surgical or percutaneous interventions to maintain their patency. On the other hand, a higher proportion of AVFs than AVGs are abandoned prior to their successful use, resulting in prolonged CVC-dependence. The superiority of AVFs over AVGs has been questioned, in particular for older (≥ 60 years) adults, who currently account for 60% of patients initiating chronic HD for treatment of ESKD [1]. Contemporary observational studies comprised of large cohorts of older adults have suggested that AVGs may confer similar or better patient outcomes than AVFs [10–12]. In an intention to treat analysis, AVGs had a higher secondary patency rate than AVFs in the first 18 months of access creation [13, 14]; shorter time to access cannulation; and lower rates of adjuvant procedures than AVFs, conferring faster transition to CVC-free HD [6, 15–17]. A meta-analysis of 13 studies concluded that older patients have a 50–65% higher risk of primary AVF failure and 80% higher risk of secondary AVF failure compared with younger patients [18].

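### The stated 80% power for a 25% effect with 5% extra variance does not follow from its inputs, and the near-Poisson variance behind it is not credible for CVC-free days

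*Protocol article*

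**What the plan says.** All the power statements are in the protocol article under 'Sample size calculation and power considerations for primary outcome'.

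- Test: "sample size calculations are based on two-sided tests with 5% type 1 error rate".
- Fistula-group rate, from the sponsor's pilot: "the average rate for CVC-free days was 15/100 patient-days among study patients who underwent AVF placement".
- Attrition: "a conservative estimate of 25% drop-out rate".
- Model and duration: "Assuming a Poisson distribution and an average follow-up of two years".
- Power claim A, under pure Poisson and stated as more than 90%: "power to detect a minimum of 5% points increase in CVC-free days in the graft group with 131 patients per group".
- Power claim B, allowing for overdispersion, with 262 patients in total and 15 per 100 in the fistula group: "we will have 80% power to detect an effect size of 25% for a 5% inflation of variance".
- Closing remark: "The power will be greater if the rate of CVC-free days is 20/100 patient-days or higher in the fistula group".

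No SD, dispersion factor or other measure of between-patient spread is given. The 'Primary outcome' section explains that a patient's CVC-free time can consist of several separate stretches with catheter dependence in between.

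**The concern.** A Poisson count has a variance equal to its mean, as if each CVC-free day were an independent event. These days are not independent. Once an access works, CVC-free days accumulate in an unbroken run; until it works, or after it fails, there are none. The Background says of fistulas that "a higher proportion of AVFs than AVGs are abandoned prior to their successful use, resulting in prolonged CVC-dependence". Such an outcome varies between patients far more than Poisson allows, and an allowance of 5% hardly changes that.

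Claim B also looks wrong on its face. About 110 expected CVC-free days per patient, with near-Poisson variance and roughly 100 or more patients per arm, should detect a much smaller effect than 25%.

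These two claims are the only printed basis for the sample size of the primary outcome. If the numbers do not connect, a reader cannot tell what difference the trial can detect, or how to interpret a null result.

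**Working it through.** **Inputs.** From the sample size section: two-sided 5% test (1.96), fistula rate 0.15 per day, 730 days, 131 per group. Removing the 25% drop-out entirely leaves 131 × 0.75 ≈ 98 per group. Both sizes are shown, because the planned analysis uses at-risk time as an offset and so keeps the time that drop-outs contribute.

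**Formula.** z = ln(RR) / √[φ(1/m₀ + 1/m₁)/n], power = Φ(z − 1.96). Here m is the expected CVC-free days per patient and φ is the variance relative to Poisson. m₀ = 0.15 × 730 = 109.5.

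**Claim B: 25% effect, φ = 1.05, stated power 80%.** m₁ = 136.875; ln 1.25 = 0.2231; 1/m₀ + 1/m₁ = 0.01644.

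- n = 98: z = 0.2231/√(1.05 × 0.01644/98) = 0.2231/0.01327 = 16.8; power about 100%.
- n = 131: z = 0.2231/0.01148 = 19.4; power about 100%.
- Patients needed for 80% power: 2.7, so 3 per arm.
- Effect detectable with 80% power: 4.0% (n = 98) or 3.4% (n = 131), not 25%.
- φ that would give 80%: (0.2231/2.8016)² × n/0.01644 = 37.8 (n = 98) or 50.6 (n = 131).

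Other readings do not recover 80% from the printed inputs. Shorter follow-up (548, 365 or 100 days), the rate-difference scale, and a negative binomial dispersion of 0.05 all leave power above 99%. Only changed inputs come close: 50-fold variance over 730 days with 131 per group gives 80.4%, and 5-fold variance over 100 days with 98 per group gives 81.4%.

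**Claim A: 15 to 20 per 100, φ = 1, stated power above 90%.** m₁ = 146; ln(20/15) = 0.2877; 1/m₀ + 1/m₁ = 0.01598.

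- n = 98: z = 22.5. n = 131: z = 26.0. Power is about 100%, so the inequality is satisfied.
- Patients needed for 90% power: 3.2415² × 0.01598/0.2877² = 2.03, so 3 per arm, which gives 97.6%.

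**What the variance assumption implies.** With φ = 1.05 the between-patient SD is √(1.05 × 109.5) = 10.7 days in 730, about 1.5 days per 100. The largest SD possible at a mean proportion of 0.15 is √(0.15 × 0.85) = 0.357, or 35.7 days per 100. Suppose a share q of patients has no CVC-free days and the rest share one Poisson mean. Then φ = 1 + 109.5q/(1 − q), and the 5% allowance is used up when q/(1 − q) = 0.05/109.5, about 1 patient in 2,200.

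**Power for 15 versus 20 on the per-patient proportion scale.** z = 0.05/(SD × √(2/n)). The SDs are assumptions.

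| Assumed SD | 98 per arm | 131 per arm |
|---|---|---|
| 0.10 | 94% | 98% |
| 0.15 | 65% | 77% |
| 0.20 | 42% | 53% |
| 0.25 | 29% | 37% |

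Eighty percent power requires an SD no larger than 0.05/(2.8016 × √(2/n)), which is 0.125 (n = 98) or 0.144 (n = 131).

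**Effect scales.** Five points on 15 is 5/15 = 33% relative; 25% of 15 is 3.75 points. The two claims concern different effects.

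**The case against.** **Claim A is not false.** It is an inequality under a stated Poisson assumption, and about 100% satisfies it. A reader might infer that neither power figure follows from its inputs; that holds only for claim B. What remains against claim A is that its inputs do not lead to 131 per group. A reader might also suspect that a relative 5% was used in place of 5 points, but the text says points and nothing in it supports that suspicion.

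**The 5% may be a misprint in a sound calculation.** If 80% is right and the true allowance was 38- to 51-fold, then φ/n = 37.8/98 = 0.386. For 15 versus 20, z = 0.2877/√(0.386 × 0.01598) = 3.66, so power is about 96%. The 5-point target would then be well covered. This cannot be excluded, and it is why the figure needs correcting before anyone concludes that the trial is too small.

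**The closing remark is defensible.** It follows the 25% statement, and for a fixed relative effect power does rise with the base rate. At φ = 40 and n = 98 a 25% effect has 78% power from 15 per 100 and 88% from 20 per 100. For a fixed 5-point difference power falls instead: 95% for 15 to 20 and 88% for 20 to 25. The remark needs a label; it is not an error.

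**The Background gives no abandonment share.** It compares fistulas with grafts without a percentage. Abandonment also need not mean zero CVC-free days, because days on a later access count. No particular overdispersion can be derived from that sentence.

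**Overdispersion is anticipated in the analysis.** Deviance checks and negative binomial models are planned. That bears on the test, not on the printed power.

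**Conclusion.** Claim B is wrong as written. Its inputs give about 100% power, not 80%, under every standard reading tried, and 80% would need a variance roughly 38 to 51 times Poisson. Claim A is true but does not explain 131 per group. Poisson variance with 5% inflation, an SD of about 1.5 days per 100, is not credible for an outcome that accrues in long stretches.

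A reader might go further and infer that real power for the 5-point target is far below 80 to 90%. The document does not support that, because it gives no between-patient SD. Power is adequate at an SD of about 0.10, moderately short at 0.15, and far short only from about 0.20. Any shortfall is conditional on the SD. The recalculation rests on a Wald test of the log rate ratio, a common 730-day follow-up, and a shared SD in both arms for the proportion-scale figures.

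**What to change.** 1. Correct or explain the 5% variance inflation, so that effect, power, dispersion and sample size agree.
2. Restate power for 15 versus 20 per 100 at a total of 262, using the per-patient SD or dispersion factor from the pilot already cited for the 15 per 100 rate. Add a short sensitivity range, for example SD 0.10 to 0.25, and say how drop-out enters the calculation.
3. Label 5 points as absolute (a 33% relative increase) and 25% as relative (3.75 points), and say that the closing remark applies to a fixed relative effect.

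This takes a short recalculation and a few sentences. It needs no change in sample size, which matters because enrolment is under way. The cost is that the stated power may become less favourable.

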### Analysis for primary outcome

The primary outcome is the rate of CVC-free days per 100 patient-days. The primary analysis will be performed under the intention-to-treat principle. The outcomes will be measured from the date of randomization to the date of an end-of-study event (see **Additional file 7**) or end-of-study date, whichever comes first. For each participant, the primary outcome will be the cumulative number of days that dialysis is delivered using AV access with the at-risk time as an offset. We will compare outcomes between the treatment groups using Poisson regression, modeling the number of CVC-free days as the dependent variable with a log link, the treatment assignment as the predictor, and the natural log of number of at-risk days as an offset. Covariate adjustment will include enrollment center and history of prior AV access. Analyses will take into account events of CVC re-use after CVC-free days. Deviance residuals and the overall deviance measure will be calculated to assess the overall goodness of fit of the model as part of model diagnostics. If we observe overdispersion, we will explore the negative binomial models. Sensitivity analyses will be performed in the as-treated and per-protocol populations.

As a supporting analysis, safety analysis will be conducted to examine severe access infections defined as infections requiring hospitalization or death caused by access infection. Rates of severe infections between AVG and AVF groups will be compared using Poisson regression models. If we observe overdispersion, we will explore the negative binomial models.

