## Methods

### Study design

This is a national, multicenter, individually-randomized, parallel-group controlled trial which targets enrollment of 262 elderly patients with ESKD with one or more coexisting medical conditions that puts the patient at higher risk of AVF maturation failure, i.e., cardiovascular disease, peripheral arterial disease and/or diabetes mellitus. Participants are randomized to surgical AVF creation vs. surgical AVG placement (Fig. 1).

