## Randomization

After informed consent is obtained, a member of the study team at each clinical center enacts the randomization through the centralized REDCap platform (Fig. 1). The randomization system is based on a block-permutation scheme with variable (two to four) block sizes, and assigns participants in a 1:1 ratio to AVG or AVF placement, stratified by (a) clinical center and (b) history of previous AV access surgery.

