## Heterogeneity of treatment effects

We will test for heterogeneity of treatment effect as a follow-on exploratory analysis whenever a main treatment effect is detected, to determine whether the intervention has different relative benefits for different subgroups. ***Subgroup analyses***. We anticipate treatment effects will vary across different patient subpopulations defined by the following cofactors: age subcategories (< 80 vs. ≥ 80 years old at the time of enrollment) [11], sex [36–38], race [39, 40], place of residence at the time of enrollment (nursing home residence vs. other) [41], presence or absence of previous AV access creation [42, 43], and location of study AV access placement (forearm or arm) [15, 44−46]. Thus, subgroup analyses will be performed, and the tests will be based on the coefficients for the interaction terms between the intervention and the subpopulation cofactors.

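### The primary model adjusts only for the two randomization strata; prespecifying age, diabetes, peripheral arterial disease and cardiovascular disease could add modest precision at little cost (optional improvement)

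*Protocol article*

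**What the plan says.** **Model.** In *Analysis for primary outcome* the article says: "We will compare outcomes between the treatment groups using Poisson regression, modeling the number of CVC-free days as the dependent variable with a log link". Treatment is the predictor and log at-risk days is the offset. On covariates: "Covariate adjustment will include enrollment center and history of prior AV access". On extra variation: "If we observe overdispersion, we will explore the negative binomial models".

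**Strata.** *Randomization* says that allocation is "stratified by (a) clinical center and (b) history of previous AV access surgery". The covariates named are therefore the strata.

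**Risk factors.** *Study design* describes cardiovascular disease, peripheral arterial disease and diabetes as "coexisting medical conditions that puts the patient at higher risk of AVF maturation failure". *Background* cites a meta-analysis in which older patients had a 50–65% higher risk of primary fistula failure than younger ones. The rationale for choosing CVC-free days lists the rate of maturation and the time to it among the events that the measure captures.

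**Availability.** Table 2 makes age and at least one of these comorbid conditions entry criteria. Table 3 schedules demographics and medical history at screening or baseline, before surgery.

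**Reuse.** The tertiary and exploratory analysis sections take covariates similar to those of the primary model. *Analysis for secondary outcomes* names none.

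**The concern.** CVC-free days will differ widely between patients. Some will stay on a catheter throughout, and others will be free of it for most of follow-up. If baseline variables predict part of that spread, a model that includes them gives a tighter interval for the rate ratio and corrects for chance imbalance between arms. The article itself gives reasons to expect such prediction from age and three comorbidities, holds the data, and does not name them for the primary model. At stake is some precision in a trial of 262 patients with an assumed 25% drop-out. The validity of the comparison is not at stake.

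**Working it through.** **1. Inputs.** From the sample size section: two-sided 5% test, 131 per group, 25% drop-out (131 × 0.75 ≈ 98 per group), 15 CVC-free days per 100 patient-days with a fistula, an increase of 5 points, and 2 years (730 days). The share of between-patient variance that the added covariates explain beyond the strata (R²) is **not in the documents**. It is assumed here to lie between 0 and 0.10.

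**2. The plan's own power figure.** SE(log RR) = √[1/(n·r₀·t) + 1/(n·r₁·t)].
- n = 131: √[1/(131 × 0.15 × 730) + 1/(131 × 0.20 × 730)] = 0.0110.
- n = 98: 0.0128.
- log(20/15) = 0.288, so power is about 100% either way. The stated >90% is met.

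The article's second figure is 80% power for a 25% effect with variance inflated by 5%. It does not follow from these inputs, which again give about 100%. Reaching 80% needs variance inflated about 38-fold (n = 98) to 51-fold (n = 131). That is a separate matter. Here 80% serves only as an illustrative starting level.

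**3. Gain as a function of R².** Residual variance is multiplied by (1 − R²), so power = Φ[(1.96 + 0.8416)/√(1 − R²) − 1.96] and equivalent sample = 262/(1 − R²).

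| Assumed R² | SE ratio | Power | Equivalent N |
|---|---|---|---|
| 0 | 1.000 | 80.0% | 262 |
| 0.02 | 0.990 | 80.8% | 267 |
| 0.05 | 0.975 | 82.0% | 276 |
| 0.10 | 0.949 | 84.0% | 291 |

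This is a linear-model approximation, so it was checked by simulation.

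**4. Simulation under a log-link count model.** Settings: 98 per arm, 730 days, rate 0.15, rate ratio 1.25, gamma heterogeneity with variance 0.30, days capped at 730, one continuous and three binary covariates, no strata in the model, 400 runs. Each cell shows the value without → with the four covariates.

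| Log rate ratio per covariate | Plain Poisson SE | Robust SE | Actual SD of estimates |
|---|---|---|---|
| 0 | 0.0130 → 0.0131 | 0.0782 → 0.0782 | 0.0817 → 0.0834 |
| 0.1 | 0.0129 → 0.0131 | 0.0811 → 0.0789 | 0.0848 → 0.0846 |
| 0.2 | 0.0127 → 0.0129 | 0.0886 → 0.0801 | 0.0873 → 0.0813 |

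The plain Poisson SE never falls. The robust SE is unchanged with useless covariates, and falls by 1 − 0.0789/0.0811 = 2.7% and 1 − 0.0801/0.0886 = 9.6% in the other two rows. The actual spread falls less: 0.2% and 6.9%. A separate simulation of a bounded, overdispersed outcome gave no loss with non-prognostic covariates and a robust SE about 1–4% smaller with moderate to strong ones. Since 1 − 0.99² ≈ 0.02 and 1 − 0.96² ≈ 0.08, that corresponds to R² of roughly 2–8%.

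**5. Chance imbalance.** For a binary covariate with an assumed prevalence of 30–50%, the SD of the difference between arms is √[2p(1 − p)/131] = 5.7 to 6.2 percentage points. With a log rate ratio of 0.2, an imbalance of 6 points shifts the log rate ratio by 0.2 × 0.06 = 0.012. Against a robust SE near 0.08 this is small.

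**The case against.** The strongest reply is that nothing here is wrong. Adjusting for the randomization strata is what the design calls for, and omitting other predictors in a 1:1 randomized trial biases nothing. That stands in full and is why the point is optional.

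Other parts also stand:
- The wording says what adjustment will include and does not close the list. A condensed article may leave further covariates to an analysis plan that is not shown.
- Every participant is at least 60 and has at least one listed comorbidity. This narrows the range of the covariates and probably lowers R².
- The comorbidity statement concerns fistulas, so these variables may predict less in the graft arm.
- Longer or different covariate lists could be defended. The four proposed here are those that the article itself ties to fistula failure.

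A reader might infer that the article names age and sex as predictors of outcome, because the heterogeneity section says "We anticipate treatment effects will vary across different patient subpopulations" and lists both. It does not: that passage concerns effect modification and is handled by interaction tests. Sex therefore has no support here as a prognostic covariate. Age rests on the *Background* meta-analysis.

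A reader might also infer that the secondary models inherit the short list. *Analysis for secondary outcomes* states no covariates, so only the tertiary and exploratory models do.

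What the reply does not remove is that the article gives its own reasons to expect prognostic value, has the data, and would lose almost nothing by using them.

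**Conclusion.** The point holds as an optional improvement. The strata-only model is valid and contradicts nothing in the article. It may give up some precision and leaves chance imbalance on likely predictors unadjusted.

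Starting from 80% power, the expected gain is nil at R² = 0, about 2 points at 5% and about 4 points at 10%. The bounded-outcome simulation points to the lower part of that range. All R² values, covariate strengths and the heterogeneity are assumptions. The gain appears only with standard errors that allow for overdispersion.

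It would be tempting to say that the plan throws away precision as a matter of fact, or that the primary result is at risk. The documents support neither: they give no prognostic strength for CVC-free days, and the model-based Poisson standard error would not shrink at all.

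**What to change.** Before anyone compares outcomes by arm, state whether the two-factor list is final. If it is, consider adding age (continuous), diabetes, peripheral arterial disease and cardiovascular disease, as recorded at baseline, as fixed covariates in the primary model beside centre and prior AV access. Use one definition for the peripheral disease covariate, because *Study design* refers to arterial and Table 2 to vascular disease.

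Base inference on sandwich or quasi-Poisson standard errors, and report the strata-only model as a sensitivity analysis. The tertiary and exploratory models that borrow the set would follow.

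The cost is a sentence or two in the analysis section and a few degrees of freedom. No new data are needed.

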### Analysis for secondary outcomes

Access-related healthcare costs analysis will be based on the intention-to-treat principle. The costs will include index access placement (AVF or AVG), procedures required to promote study AV access maturation (angioplasty or surgical revision), procedures to maintain study AV access patency for HD after successful use (angioplasty, thrombectomy, or surgical revision), surgery to place a new vascular access (AVF or AVG) if the study AV access failed or was abandoned, procedures to promote maturation and maintain patency of all subsequent accesses, procedures of CVC exchange due to catheter dysfunction or infection, and reimbursement associated with access-related hospitalizations. Similar to our previous work, we will use the reimbursement fees established by the Center of Medicare and Medicaid Services, per each corresponding year of study, for access-related hospitalizations and inpatient or outpatient services and procedures [34]. Per-patient access cost will include the cost of all access-related procedures and hospitalizations divided by the total number of years of follow-up for that patient. As in standard economic analysis, costs will be discounted at 3% annually. Log transformation will be used to better approximate normality. A general linear model will be used to test the difference on the log scale between the fistula and graft groups. The estimates will be back transformed to represent median costs on the original scale. We will also use a generalized linear model with Gamma distribution and a log link to compare the mean access-related cost between the two groups.

Other secondary outcomes include rates of AV access maturation, rates of AV access adjuvant procedures, and rates of infectious and non-infectious vascular access (CVC or AV access) complications. Poisson regression models will be used to test the difference between AVF and AVG groups. If we observe overdispersion, we will explore the negative binomial models. Deaths will be analyzed using Cox regression models.

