### Secondary, tertiary and other outcomes

The secondary outcome will compare vascular access-related healthcare costs; rates of AV access maturation; rates of AV access adjuvant procedures; rates of infectious and non-infectious vascular access (CVC or AV access) complications; and deaths. Event definitions for AV access outcomes and CVC outcomes, and cause of death categorization are listed in **Additional file 4**. Standard costs attributed to vascular access (index AV access, CVC, new AV access) adjuvant interventions and complications will be used to calculate cumulative access-related costs between the two groups (**Additional file 5**).

Tertiary outcomes consist of patient-reported outcomes. Patients’ satisfaction with their dialysis vascular access will be elicited with the Vascular Access Questionnaire [21] and the Decision Regret Scale [22]. Health-related quality of life will be assessed with the EuroQol 5-dimension 3-level [23]. Patient’s preferences between quality/quantity of life and future/present health will be assessed with the Attitude Scale [24] and SUPPORT questionnaire [25]. These instruments are described in **Additional file 6**.

Exploratory outcomes will evaluate for relationships between preoperative frailty measures and the rate of index AV access primary failure, time to successful AV access cannulation, and the rate of adjuvant procedures on index AV access.

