## Participant timeline

Recruitment is projected over 2.5 years. We target an average follow-up period of 2 years from the date of randomization.

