## Trial status

This clinical study is currently in the enrollment phase. Enrolment started in June 2022, and the estimated completion date is the end of 2026. The study protocol uses the current version 4.4, dated October 28, 2020. The change history is given in the “Ethics and legal considerations” section.

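### Access costs are discounted at 3% but divided by undiscounted years and priced at each year's own fees, so the per-year cost drifts with follow-up length and calendar date; the effect on the between-arm ratio is about 1%

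*Protocol article*

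**What the plan says.** The Protocol article, under Analysis for secondary outcomes, sets three rules for the per-patient access cost.

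- **Prices:** "we will use the reimbursement fees established by the Center of Medicare and Medicaid Services, per each corresponding year of study". No common price year is named.
- **Annualization:** the sum of all access-related procedures and hospitalizations is "divided by the total number of years of follow-up for that patient".
- **Discounting:** "As in standard economic analysis, costs will be discounted at 3% annually". The sentence applies to costs. It gives no base date, does not say whether discounting is continuous or in yearly steps, and does not extend to the years of follow-up.

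The resulting cost is compared between arms on the log scale and back-transformed to medians. A Gamma model with log link is also planned for the means.

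**The concern.** Discounting belongs to a total: it expresses costs incurred at different times as one present value. A cost per year is a rate. Discounting the numerator and leaving the denominator in plain years gives a quantity that is neither. Two patients who use the same resources every year get different annual costs only because one was followed for longer.

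Pricing at each year's own fees adds a second time effect. Unless fees are later re-based, the same procedure enters at different amounts in different calendar years, and fee changes partly offset or reinforce the discount.

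At stake are the cost figures to be reported for each strategy and how far individual patients' costs can be compared. These rules are stated in the article, so this is not a complaint about missing detail.

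**Working it through.** **Plan's own figure.** The article states no cost figure and no power for the cost outcome, so there is nothing to reproduce.

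**Inputs**
- Discount rate 3% a year, on costs only (Analysis for secondary outcomes).
- Follow-up that varies between patients. Participant timeline: "Recruitment is projected over 2.5 years" and "We target an average follow-up period of 2 years from the date of randomization". The sample size section assumes 25% drop-out, and the footnotes to Table 3 end follow-up at death, transplantation, transfer of care and other events.
- Longest possible follow-up of about 4.5 years, for the earliest enrollees only. Trial status: "Enrolment started in June 2022, and the estimated completion date is the end of 2026".
- Assumptions made here: constant resource use of 1 cost unit per year, and discounting from randomization. Annual fee change g is not given; a range of −3% to +5% is used.

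**Step 1: follow-up length, constant fees.** With continuous discounting over T years, the plan's rule gives

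(1 − 1.03^−T) / (T × ln 1.03), where ln 1.03 = 0.02956.

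At T = 2 this is (1 − 0.9426) / 0.0591 = 0.971. With yearly steps and year 1 undiscounted, T = 2 gives (1 + 1/1.03) / 2 = 0.985.

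| Follow-up (years) | Continuous | Yearly steps |
|---|---|---|
| 0.5 | 0.993 | 1.000 |
| 1 | 0.985 | 1.000 |
| 2 | 0.971 | 0.985 |
| 3 | 0.957 | 0.971 |
| 4.5 | 0.936 | 0.950 |

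The correct value in every row is 1.000. A half-year patient appears 1.5–2.2% dearer per year than a 2-year patient with identical use, and 5.3–6.0% dearer than a 4.5-year patient.

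**Step 2: calendar date.** Take two patients with equal follow-up and use, randomized 2.5 years apart. Their annual costs differ by (1 + g)^2.5 − 1:

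| Fee change per year (assumed) | Difference |
|---|---|
| −3% | −7.3% |
| 0% | 0 |
| +1% | +2.5% |
| +3% | +7.7% |
| +5% | +13.0% |

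If fees rose by exactly 3% a year, the follow-up effect of Step 1 would cancel, but the enrolment-date effect would remain.

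**Step 3: between arms.** Using the continuous factors at each arm's mean follow-up:
- 2.0 versus 1.5 years: 0.9782 / 0.9710 = 1.007, a shift of 0.7% in the cost ratio.
- 2.0 versus 1.0 years: 0.9854 / 0.9710 = 1.015, a shift of 1.5%.

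**Step 4: consistent rule.** Discounted years are (1 − 1.03^−T) / ln 1.03, which is 0.496 at T = 0.5, 1.942 at T = 2 and 4.214 at T = 4.5. Dividing discounted cost by these, or discounting neither, at one price year gives exactly 1.000 for every T and every enrolment date.

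**The case against.** The strongest reply is that the trial compares arms, and the comparison hardly moves. Randomization is 1:1 in blocks of two to four within center and prior-access strata, so enrolment date, and with it the fee year, is close to balanced. That stands. A reader might infer from the Discussion, which expects grafts to cost less early and possibly more late, that these distortions bias the comparison. The article does not support this: giving later costs less weight is what discounting is for, and Step 3 puts the shift from the mismatched denominator at about 1% unless follow-up differs strongly by arm.

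Second, year-specific fees suit the insurer perspective stated in Table 1, since the insurer pays the fee then in force. Re-basing to one price year might also appear in Additional file 5 or an analysis plan that is not shown. This weakens the price-year part, which is conditional on fees changing and not being re-based. It does not touch the mismatch between discounted costs and plain years.

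Third, a reader might see a contradiction with Secondary, tertiary and other outcomes, which speaks of "Standard costs attributed to vascular access". None is claimed. That phrase fits a standard tariff applied to each event, and a Medicare fee schedule is one whether or not it is updated yearly.

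Fourth, the 5–6% figure contrasts extreme patients. That also stands: the end of 2026 is the completion date, so only the earliest enrollees could approach 4.5 years.

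**Conclusion.** The point holds as a minor inconsistency in how a secondary outcome is defined. On the plain reading of the article, the reported annual cost is understated by about 1.5–3% at the 2-year average follow-up and by 5–6% at the maximum of about 4.5 years, with the range set by the unstated discounting convention. These figures assume constant use. Costs concentrated early, such as the index surgery, are discounted less.

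The calendar-year effect is real only if fees change and are not re-based, and its size and sign are unknown. The graft-to-fistula ratio shifts by 0.7% for mean follow-up of 2.0 versus 1.5 years and by 1.5% for 2.0 versus 1.0 years. The cost levels and their comparability between patients are affected; the cost conclusion is not threatened.

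**What to change.** In Analysis for secondary outcomes, make two changes before analysis.

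1. Either drop discounting for the per-year cost, or divide discounted cost by follow-up years discounted at the same rate, from the same base date and under the same convention. State which. The two options agree exactly only when use is constant over time.
2. Value all events from all years with one reference-year Medicare fee schedule, or re-base each year's fees to one named price year.

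The cost is one or two sentences and a single fee table in place of several, with no new data. The small downside is that the costs will no longer equal the amounts actually reimbursed in each year.
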